### Patient exclusion criteria

Other neurological, orthopaedic, or cardiopulmonary problems that in the view of the researchers may interfere with participation.Cognitive impairment defined as a Mini Mental State Examination (MMSE) score of less than 24.Insufficient motivation for participation.

### Intervention

Two treatment conditions are investigated in this study: the experimental condition (BEWARE) and the TAU (physical therapy). Both interventions consist of 12 sessions, each 1 hour long, two times per week for 6 weeks. All treatment sessions occur at the same time of day on the same two days of the week (Monday and Thursday) throughout the study. The treatment groups consist of six patients, in both conditions.

#### Experimental condition: body awareness training (BEWARE)

The experimental intervention is delivered by professionals from the fields of psychology, physical therapy, and psychiatry. The BEWARE training is based mainly on the principles of ACT [37]. The goals of this training are to acquire and apply adequate coping strategies with wearing-off and live a valuable life despite the presence of wearing-off symptoms.

In the first therapy session, psycho-education about PD and wearing-off is discussed by the psychiatrist. In the following sessions, the psychologist explains and provides training in the concepts of body awareness, cognitive defusion, and valued living and prepares the patients for the imaginary exposure. Body awareness is achieved by using attentional exercises. Cognitive defusion techniques attempt to change the way the patient interacts or relates to thoughts, by observing one’s thoughts in a non-judgemental manner. In ACT, valued living is achieved by choosing personal life directions while undermining choices based on avoidance or social compliance.

Imaginary exposure, in ACT therapy known as FEEL (Feeling Experiences Enriches Living) exercises [37], is applied during sessions 6 to 12. During the imaginary exposure, patients are asked to imagine a real-life situation that easily triggers wearing-off. The patients practice with experiencing and daring to allow the feelings that are triggered by the ‘off’ during this imaginary exposure. Throughout these sessions, the ‘off’ situations become more challenging and patients are encouraged to gradually take part in activities that they previously avoided because of the (anticipation of) wearing-off.

The psychological exercises are alternated by physical exercises that are performed by the physical therapist. These exercises include strategies for starting and performing complex movements with risk of falling, such as sitting down and rising from a chair, called transfers. Also, standing, initiation of walking, and walking in complex or stressful situations are addressed. Lastly, moving to rhythmic music helps the patients to relieve stress after the imaginary exposure. These aspects teach the patient to be able to cope with wearing-off situations. To generalize the intended effect, the patients are given homework assignments, such as body awareness exercises and planning value-based committed actions in daily life.

#### Control condition: treatment as usual

The patients in the control group receive TAU based on the current KNGF (Royal Dutch Society for Physical Therapy) guidelines for physical therapy in patients with PD [38]. The group treatment contains exercises for balance, walking, posture, reaching and grasping, strength, flexibility, relaxation, and physical condition. As in the experimental condition, patients are taught strategies on how to make transfers.

### Outcome measures

#### Primary outcome measure

The primary outcome measure is self-efficacy, assessed with the 10-item General Self-Efficacy Scale (GSES) [39]. Self-efficacy is defined as the extent or strength of one’s belief in one’s own ability to complete tasks and reach goals (in other words, a person’s belief in his or her ability to succeed in a particular situation) [40]. In this questionnaire, patients are asked to rate specific statements on a scale from 1 to 4 (1 = not at all true, 2 = hardly true, 3 = moderately true, and 4 = exactly true). The GSES has proven to be a valuable and reliable outcome measure in patients with PD [41].

#### Secondary outcome measures

The Parkinson’s Disease Questionnaire-39 (PDQ-39)

This questionnaire is a measure of quality of life adapted for people with PD [42]. It consists of 39 statements that cover eight domains associated with health, such as mobility and emotionality, that can be influenced by PD. Patients can reply by ticking the relevant answer that indicates whether they experienced problems during the past month (five boxes from ‘never’ to ‘always’). The PDQ-39 is a valid and reliable instrument for patients with PD [42, 43].2.The Wearing-off Questionnaire 19 (WOQ-19)

In this 19-item questionnaire [35], patients with PD indicate which symptoms they experience and whether these symptoms improve after administration of PD medication.3.Beck Anxiety Inventory (BAI)

This self-report questionnaire consists of 21 common symptoms of anxiety [36]. Patients indicate how much they have been bothered by these symptoms during the past week, including today.4.Beck Depression Inventory

This 21-item self-report questionnaire measures whether patients experience depressive symptoms [44]. Patients indicate the statements that are most applicable to their own situation during the past week, including today.5.10-Meter Walk Test (10MWT)

To measure comfortable walking speed, the patients are asked to walk 10 metres, which are characterized by a starting and a finishing point [45]. The researcher measures the time needed to cover this distance.6.Timed One-Leg Stance Test (OLST)

This test measures balance by asking the patients to stand on one leg without help [46]. The number of seconds that the patients maintain their balance is noted; the maximum is 60 seconds.7.The Nottingham Extended Activities of Daily Living (NEADL) index

This 22-item self-report questionnaire covers four aspects of daily living: mobility, activities in the kitchen, domestic tasks, and leisure activities [47]. Patients indicate whether they independently performed activities during the past weeks.8.Freezing of Gait (FOG) questionnaire

This six-item questionnaire is used to identify current problems with walking and symptoms of freezing [48]. For each item, patients indicate which of the five statements is most applicable.9.Visual Analogue Scales (VASs)

Before and after each therapy session, patients indicate how they are feeling at the actual moment by using 10 VASs. Patients put a cross on a line of 10 cm with extreme feelings at the edges (for example, ‘relaxed’ or ‘tense’ ,  ‘in control’ or ‘out of control’ , and ‘happy’ or ‘sad’).

### Patient researchers

Because the experimental treatment is a new approach, the opinion and experiences of the participating patients are considered very important. Therefore, two patient researchers of the Dutch Parkinson patient association (Parkinson Vereniging) contribute to the study by anonymously documenting the patients’ expectations and evaluation points for qualitative analysis. Prior to and directly after the intervention period, a semi-structured group interview takes place in which the patients are asked questions related to the study and can share their experiences and suggestions for adaptations in future studies or in the implementation phase. This interview is with the patients (both participants and researchers) only.

### Statistical analysis

#### Calculation of sample size

We expect that, compared with the TAU group, the experimental group will show a 10 % larger improvement on the GSES after treatment. Nieuwboer et al. [49] investigated a 3-week physical home training program and showed that physical measures improved with 4.2–5.5 % compared with 3 weeks of no therapy. Because we expect the effects of the combination of physical therapy and ACT in the BEWARE intervention to be stronger and the intervention period to be longer and more intensive, we hypothesize a larger difference in our primary outcome measure. Considering this study and data on the GSES in other chronic diseases [50], we expect to detect a 10 % larger reduction in GSES score from 32 to 28.8 and an overall standard deviation of 3.3. A minimum of 16 patients is required per arm of the trial. With that, including a dropout of 10 %, we estimate that 36 patients with PD (18 per arm) are needed to achieve a sufficient statistical power of 80 % with two-tailed significance level set at a *P* value of less than 0.05.

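### The stated minimum of 16 evaluable patients per arm gives about 76% to 78% power on the plan's own inputs, not 80%

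*Protocol article*

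**What the plan says.** All the inputs stand in the protocol article under Calculation of sample size.

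- Effect: "we expect to detect a 10 % larger reduction in GSES score from 32 to 28.8", a difference of 3.2 points.
- Spread: "an overall standard deviation of 3.3".
- Level: "two-tailed significance level set at a" *P* value below 0.05.
- Evaluable number: "A minimum of 16 patients is required per arm of the trial".
- Dropout and total: the number is raised, "including a dropout of 10" per cent, and the section concludes that "36 patients with PD (18 per arm) are needed to achieve a sufficient statistical power of 80" per cent.

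The section does not name the test or formula behind the 16, and it gives no correlation between baseline and later scores. Under Data analysis, the article plans a repeated-measures analysis of variance with two groups and three time points, and multiple imputation of missing data.

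**The concern.** The section gives everything needed to recompute a two-group comparison of means, and the recomputed minimum is larger than 16 under either standard formula. A number called a minimum for 80% power has to reach 80%, so 16.69 cannot be rounded down. The dropout step then builds on the low figure: 18 randomised per arm is what 16 evaluable requires, not what 17 or 18 evaluable requires.

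At stake is how the result is read. In a trial of 36 patients, a null finding will be judged against the stated power. If the type II risk at the planned evaluable number is 22% to 24% rather than 20%, the article should say so.

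**Working it through.** **Inputs** (all from Calculation of sample size): difference 32 − 28.8 = 3.2; SD 3.3; two-sided alpha 0.05; power 80%; 1:1 allocation; dropout 10%. Standardised difference d = 3.2 / 3.3 = 0.970. Only the size of the difference enters, not its direction.

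**1. The plan's figure, normal approximation.** n per arm = 2 × (1.960 + 0.842)² / d² = 16.69, so 17 when rounded up. The plan's 16 equals this result rounded down; since the formula is not named, that is the likely origin rather than a documented one. A one-sided 5% level would give 13.15, so 14, which fits less well and contradicts the two-tailed statement.

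**2. Power at 16, 17 and 18 evaluable per arm.** Normal approximation: power = Φ(d × √(n/2) − 1.960). Two-sample t-test: noncentral t with 2n − 2 degrees of freedom and noncentrality d × √(n/2).

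| Evaluable per arm | d × √(n/2) | Power, normal | t critical value (df) | Power, t-test |
|---|---|---|---|---|
| 16 | 2.743 | 78.3% | 2.042 (30) | 75.6% |
| 17 | 2.827 | 80.7% | 2.037 (32) | 78.3% |
| 18 | 2.909 | 82.9% | 2.032 (34) | 80.7% |

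The smallest number reaching 80% is 17 (normal) or 18 (t-test).

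**3. Dropout, n / (1 − 0.10).**
- The plan: 16 / 0.9 = 17.8, so 18 per arm, 36 in total. This step is correct.
- From 17: 17 / 0.9 = 18.9, so 19 per arm, 38 in total.
- From 18: 18 / 0.9 = 20 per arm, 40 in total.

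**4. What 16 evaluable per arm would support at 80% power.** With SD 3.3, the detectable difference is 3.38 points (t-test) or 3.27 (normal). With a difference of 3.2, the SD would have to be 3.13 (t-test) or 3.23 (normal).

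**5. Use of the baseline.** The article gives no correlation r between baseline and week-6 scores, so the values of r below are assumptions. If 3.3 is the SD of a single score, baseline adjustment multiplies it by √(1 − r²) (t-based power, 29 df), and a change-score comparison multiplies it by √(2(1 − r)) (30 df). Power with 16 per arm:

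| Assumed r | Baseline-adjusted | Change score |
|---|---|---|
| 0.3 | 79% | 61% |
| 0.4 | 82% | 68% |
| 0.5 | 86% | 76% |

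If 3.3 is instead the SD of the change, the figures in step 2 apply to a change-score comparison as they stand.

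**The case against.** The strongest reply is that the article names no test, and that the gap depends on which one is assumed. Under the normal approximation the plan is one evaluable patient per arm and less than two percentage points short, well inside the uncertainty of an SD taken partly from other chronic diseases. This stands. It is why the result has to be given as a range, and why the point is not a grave one. It does not make 16 correct, because both formulas put it below 80%.

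The second reply is that the planned analysis uses the baseline and could be more powerful than a post-treatment comparison. It could: baseline adjustment passes 80% with 16 per arm at an assumed correlation of 0.4. A change-score comparison at the same correlation gives about 68%. Without a stated correlation, the planned analysis neither rescues the figure nor condemns it.

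The third reply is that the 80% is attached to 36 patients and that missing data will be imputed. With all 18 per arm observed, t-test power is indeed 80.7%. But the section itself allows for 10% dropout, and imputation does not restore the information in outcomes that were never observed.

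A reader might infer that the inputs prove a power of exactly 76% and a requirement of 40 patients. The article does not support that, since those figures hold only for the t-test. A reader might also infer that the dropout step is wrong or that the trial must enlarge. The inflation from 16 to 18 is correct, and nothing here calls for more patients.

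**Conclusion.** The concern holds as a correction of the stated figure. For a two-sample comparison with the plan's inputs, 16 evaluable per arm gives 75.6% (t-test) to 78.3% (normal approximation). Reaching 80% takes 17 to 18 evaluable, or 19 to 20 randomised, per arm at 10% dropout. The planned 18 per arm meet 80% by t-test only without any dropout; by the normal formula they could lose one patient per arm.

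This rests on reading 3.3 as the SD of the quantity compared, on independent patients, and on no gain from the baseline. Both arms are treated in groups of six; any clustering from that is a separate matter and is not in these figures. It would be tempting to conclude that the trial is underpowered under its own planned analysis. The article does not allow that conclusion, because the correlation that decides it is not given. Severity is minor to moderate: the shortfall is 2 to 4 percentage points and does not affect the conduct or validity of the trial.

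**What to change.** Keep the total of 36 and restate the result, for example: *16 evaluable patients per arm give about 76% power (two-sample t-test, two-sided 5% level) for a difference of 3.2 points with SD 3.3, or 80% power for a difference of about 3.4 points, ignoring therapy-group clustering.*

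Alternatively, base the calculation on a baseline-adjusted comparison at week 6, name that analysis, say that 3.3 is the SD of a single score if that is meant, and state and justify the assumed correlation. With 16 per arm this would give about 79%, 82% or 86% power at correlations of 0.3, 0.4 or 0.5.

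The cost is a corrected sentence. The first option also means a slightly less favourable stated power; the second means committing to a correlation that the article does not now give. Neither needs extra patients.

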#### Data analysis

To promote data quality, double data entry will be used. Multiple imputation will be applied on missing data. Analysis of variance with repeated measures will be used for normally distributed outcomes at interval and ratio level. Friedman’s non-parametric repeated measures test will be applied for outcomes with non-interval or ratio scale level or for non-normally distributed variables. Factors in the analysis will be group (two levels: control and experimental) and time (three levels: baseline, assessment at week 6 (directly post-treatment), and assessment week 18 (3-month follow-up)).

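### The trial is sized on one between-arm GSES difference after treatment, but the stated repeated-measures ANOVA addresses it only through a 2-df group-by-time interaction with baseline as a time level

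*Protocol article*

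**What the plan says.** All references are to the protocol article.

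- **Calculation of sample size.** The expectation is that "compared with the TAU group, the experimental group will show a 10 % larger improvement on the GSES after treatment". The figures are a "10 % larger reduction in GSES score from 32 to 28.8 and an overall standard deviation of 3.3". From these the article concludes: "A minimum of 16 patients is required per arm of the trial". Power is 80% at a two-sided 5% level, and with 10% dropout the total is 36.
- **Study design.** Assessments are before treatment and at 6 weeks, directly after it. Week 18 is described as the long-term assessment. Read together with the sample-size text, the sized contrast is at week 6, although that text names no week.
- **Data analysis.** "Analysis of variance with repeated measures will be used for normally distributed outcomes at interval and ratio level". The factors are group (two levels) and time (three levels: baseline, week 6, week 18). Also: "Multiple imputation will be applied on missing data".
- **Background (last paragraph).** The hypothesis is that BEWARE improves self-efficacy more than physical therapy alone.

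**The concern.** The sizing rests on one number, the difference between arms after treatment. The stated model has no omnibus term equal to that number. The hypothesis concerns differential improvement, and in this model that is the group-by-time interaction. With three time levels the interaction has 2 degrees of freedom and asks only whether the arm difference is the same at all three visits. A significant result does not say which arm did better, at which visit, or by how much. Its power also depends on the week-18 difference, which the sample-size text does not mention.

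Baseline GSES enters as one level of the outcome and not as a covariate. The interaction does use it, through change over time, but less efficiently than covariate adjustment when visits are only moderately correlated. With 36 patients there is little power to spare, and a primary result without a direction or an estimate would be hard to use.

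**Working it through.** **Inputs from the article:** difference 32 − 28.8 = 3.2; SD 3.3; 16 per arm before dropout; two-sided 5%; power 80%; dropout 10%. **Assumptions, not in the article:** one correlation r between any two visits (0.3 to 0.8 examined) with equal variances, and a week-18 effect that is fully kept (3.2), halved (1.6) or lost (0).

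**1. Reproduce the stated sample size.** Two-group comparison of means at one time point:

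n = 2 × [SD × (1.960 + 0.8416) / difference]² = 2 × [3.3 × 2.8016 / 3.2]² = 16.69, so 17 per arm. This is within one patient of the stated 16.

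Dropout: 16 / 0.9 = 17.8, so 18 per arm and 36 in total, as stated. The figure therefore reproduces with no baseline term and no repeated measures.

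Power of the unadjusted week-6 t-test at 16 per arm: noncentrality 3.2 / (3.3 × √(2/16)) = 2.743 on 30 df, giving 76%. At 18 per arm it is 81%.

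**2. Group-by-time interaction.** Let D be the arm differences at baseline, week 6 and week 18. The noncentrality is

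λ = (n/2) × Σ(D − mean D)² / [SD² × (1 − r)], on 2 and 2 × (2n − 2) = 60 df.

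- Kept: D = (0, 3.2, 3.2), mean 2.133, sum of squares 6.827.
- Lost: D = (0, 3.2, 0), mean 1.067, sum of squares 6.827.
- Halved: D = (0, 3.2, 1.6), mean 1.6, sum of squares 5.12.

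At r = 0.5, with SD² = 10.89: kept or lost, λ = 8 × 6.827 / 5.445 = 10.03, power 80%; halved, λ = 8 × 5.12 / 5.445 = 7.52, power 67%. An effect that persists and one that vanishes give the same λ, so the test cannot tell them apart.

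**3. Week-6 ANCOVA with baseline as covariate.** Residual SD = 3.3 × √(1 − r²). At r = 0.5 this is 2.858, so the noncentrality is 3.2 / (2.858 × √(2/16)) = 3.167 on 29 df, power 86%. The formula ignores chance baseline imbalance and is slightly optimistic; simulation (4,000 trials per scenario) at r = 0.5 gave 84 to 86%.

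**4. Power at 16 per arm:**

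| r | Interaction, effect kept or lost | Interaction, effect halved | Week-6 ANCOVA | Unadjusted week-6 t-test |
|---|---|---|---|---|
| 0.3 | 64% | 51% | 79% | 76% |
| 0.5 | 80% | 67% | 86% | 76% |
| 0.6 | 88% | 77% | 91% | 76% |
| 0.7 | 96% | 88% | 96% | 76% |
| 0.8 | 99.5% | 97% | 99% | 76% |

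Against ANCOVA, the interaction loses about 15, 7 and 0.5 points at r = 0.3, 0.5 and 0.7 if the effect is kept or lost, and about 28, 20 and 8 points if it halves. With all 18 per arm evaluable the pattern is the same: interaction 70, 85 and 97% (kept or lost) or 57, 72 and 92% (halved), against 84, 90 and 98% for ANCOVA.

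**The case against.** The strongest reply has four parts.

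- **The interaction is a legitimate test of differential improvement, and it uses baseline.** This stands. A reader might infer that baseline is ignored or that the analysis is invalid. It is neither: under randomisation both approaches are valid, and ANCOVA is more efficient.
- **The loss is measured against ANCOVA, not against the plan.** This stands in part. At r of 0.5 or more with the effect kept or lost, the interaction is no weaker than the unadjusted t-test that reproduces the sample size (80% or more against 76%). It falls below that test at r = 0.3, or at r = 0.5 if the effect halves. The article gives neither the correlation nor the week-18 effect, so one cannot say that power falls short of plan.
- **A full analysis plan may name the decisive contrast.** It may. However, the article itself fixes the model, the factors and baseline as a time level, and those choices do not match its sizing. That is a stated mismatch and not only an omission.
- **Week 6 is inferred.** This is true; it follows from the Study design section and is a sound reading.

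Two stronger readings are not supported. A reader might infer that the group main effect, which averages in baseline, could be declared the primary result, or that success on either term would count and inflate the type I error. The article states no such rule. A reader might also infer that ANOVA tests cannot be pooled after multiple imputation. Pooling rules for multi-parameter tests exist, so the planned imputation is no obstacle.

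**Conclusion.** The point holds as a mismatch between the sizing and the stated analysis. The between-arm term that addresses the hypothesis is a 2-df omnibus interaction. It is not the single contrast used for sizing and yields no direction, timing or estimate. Compared with a baseline-adjusted week-6 analysis, the avoidable power loss is about 7 to 15 points at r of 0.3 to 0.5 if the effect is fully kept or lost, and about 8 to 28 points at r of 0.3 to 0.7 if it halves. It is negligible at r of 0.7 or more when the effect is fully kept or lost. These sizes rest on the assumed correlation structure and week-18 patterns. The mismatch itself does not. The plan should be changed because the better analysis uses data already collected, not because the trial is shown to be underpowered.

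**What to change.** Name one primary test: the BEWARE minus TAU difference in GSES at week 6, with its 95% CI. Estimate it by ANCOVA with baseline GSES as covariate, or take the week-6 contrast from a mixed model with weeks 6 and 18 as outcomes and baseline GSES as covariate. Make week 18 secondary. Multiple imputation may stay as planned.

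No extra patients, visits or measurements are needed, since baseline GSES is already collected. The one cost is procedural: the Trial status section says that data collection started in January 2014, so the change needs a documented amendment made before unblinding.

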To address both the physical and the mental aspects of PD, Wahbeh et al. [27] reviewed mind-body interventions in the treatment of PD and showed that participating in tai chi classes improved the patients’ physical condition. Landsman-Dijkstra et al. [28] tested a highly structured and standardized 3-day body awareness program in 14 participants who had chronic non-specific psychosomatic symptoms. Increases of body awareness, self-efficacy, and quality of life were found after the intervention. However, the researchers did not implement a control group in this study.

Mindfulness-based therapies have proven to be effective in many patient groups, such as patients with chronic pain, anxiety, and depressive disorders, by improving psychological functions and reducing pain and stress [29, 30], although the mean effect size was small (0.42) [30]. In addition, Åkerblom et al. [31] showed that pain-related acceptance is the strongest mediator in CBT treatment in patients with chronic pain. The authors conclude that targeting of acceptance in treatment may lead to further improvements in outcome measures. It has been shown that CBT is effective in PD patients even after a follow-up period on anxiety and coping measures [32]. Because PD is a chronic disease and is accompanied by both physical and mental symptoms (motor and non-motor symptoms), combining mindfulness-based therapy with physical rehabilitation might be of potential benefit for PD patients with WRA.

BEWARE is an integrated body awareness intervention, combined with ACT, in which mindfulness training is incorporated with physical therapy. We will test the effectiveness of this intervention—compared with treatment as usual (TAU)—in terms of self-efficacy in PD patients with WRA. We hypothesize that the BEWARE intervention will be more effective than physical therapy alone (TAU) in improving self-efficacy.

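### The non-parametric branch relies on Friedman's test, which has no group factor, so outcomes sent there (possibly the primary GSES) cannot compare BEWARE with TAU

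*Protocol article*

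**What the plan says.** The Data analysis section of the protocol article sets out two branches.

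- Parametric: "Analysis of variance with repeated measures will be used for normally distributed outcomes at interval and ratio level".
- Non-parametric: Friedman's "non-parametric repeated measures test will be applied for outcomes with non-interval or ratio scale level or for non-normally distributed variables".

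It then states, without separating the branches: "Factors in the analysis will be group (two levels: control and experimental) and time". Time has three levels: baseline, week 6 and week 18.

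The hypothesis at the end of the Background is a comparison between arms: "the BEWARE intervention will be more effective than physical therapy alone (TAU) in improving self-efficacy". The sample-size section also rests on a between-arm difference in GSES. Under Primary outcome measure, the GSES is a 10-item scale on which "patients are asked to rate specific statements on a scale from 1 to 4". The article does not say which branch the GSES takes, and it names no non-parametric method that compares the arms.

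**The concern.** Friedman's test is a one-factor, within-patient test. It can ask whether scores differ across visits. It cannot ask whether that difference depends on arm. The plan therefore assigns it a factor that it cannot hold.

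In practice the analyst would have two ways to run it, and neither answers the trial's question:

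- **All patients pooled.** The test shows whether the whole sample changed over time. Both arms receive active group therapy, so a common improvement is plausible and could be mistaken for a treatment effect.
- **Each arm separately.** This invites the reading that BEWARE worked because its p-value is below 0.05 and TAU's is not. A difference in significance is not a test of the difference between arms.

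Several outcomes could land here: the one-leg stance test (capped at 60 seconds), the WOQ-19, the NEADL and freezing-of-gait questionnaires, and the BAI, whose baseline is truncated because entry requires a score above 26. The GSES could too. It is a sum of ten four-category items with a maximum of 40, and its route depends on a judgement about scale level and on how its distribution looks in a small sample once the data are in.

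**Working it through.** **1. The planned comparison is between arms.** Inputs from Calculation of sample size: difference 32 − 28.8 = 3.2, SD 3.3, two-sided α 0.05, power 80%.

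n per arm = 2 × [3.3 × (1.960 + 0.8416) / 3.2]² = 16.69, so 17. The stated figure is 16, which is close enough to show that a two-arm comparison of means was intended. With 10% dropout, 16 / 0.9 = 17.8, so 18 per arm and 36 in total, as stated.

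**2. What Friedman's test computes.** With N patients and k = 3 visits, each patient's three scores are ranked 1 to 3 and the ranks are summed by visit (R₁, R₂, R₃). Without the tie correction,

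Q = 12 / [N k (k + 1)] × ΣR² − 3N(k + 1) = ΣR² / N − 12N.

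Arm appears nowhere in this formula. As a check, arm membership was shuffled in a simulated set of 36 patients; the statistic was 0.222 with p = 0.895 both before and after.

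**3. A hand example, 18 per arm.**

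- *Arms move in opposite directions.* Every BEWARE patient is lowest at baseline and tied afterwards (ranks 1, 2.5, 2.5). Every TAU patient is highest at baseline and tied afterwards (3, 1.5, 1.5). The rank sums are 18 + 54 = 72, 45 + 27 = 72 and 72. Q = 3 × 72² / 36 − 12 × 36 = 432 − 432 = 0. The arms differ completely and the test sees nothing.
- *Arms move identically.* All 36 patients have ranks 1, 2.5, 2.5. The rank sums are 36, 90 and 90. Q = (1,296 + 8,100 + 8,100) / 36 − 432 = 486 − 432 = 54. There is no arm difference and the statistic is very large.

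**4. Size in a trial like this one.** Simulation with 18 per arm, 3,000 trials per row, baseline mean 28.8 and SD 3.3. The change was applied at both later visits; scores were rounded and limited to 10–40. Equal correlation between visits was assumed at 0.5 and 0.7, because the article gives none. Entries are % of trials with p < 0.05, at correlation 0.5 / 0.7. Mann-Whitney on change from baseline to week 6 is shown as a test that does compare the arms.

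| True change, TAU / BEWARE | Pooled Friedman | Friedman by arm: exactly one arm significant | Mann-Whitney on change |
|---|---|---|---|
| 0 / 0 | 5.6 / 4.6 | 10.0 / 10.3 | 4.9 / 4.8 |
| +2 / +2 | 90.6 / 99.3 | 48.8 / 28.6 | 4.7 / 4.2 |
| +3.2 / +3.2 | 100 / 100 | 9.6 / 0.5 | 4.7 / 4.8 |
| 0 / +3.2 | 62.5 / 80.7 | 90.2 / 94.3 | 77.5 / 93.6 |
| −1.6 / +1.6 | 3.3 / 2.6 | 49.1 / 47.9 | 77.3 / 93.9 |

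The first three rows have no treatment effect; the last two have a true difference of 3.2.

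Repeat runs with 16 to 18 per arm agree. For equal 2-point gains at correlation 0.5, pooled Friedman was significant in 85–91%, exactly one arm in 46–53%, and BEWARE alone in 23–25%. At correlation 0.7 the corresponding figures were 98–99%, 28–35% and 15–18%.

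**The case against.** **The GSES will probably go to ANOVA.** The sample-size section plans it with means and an SD, which treats the total as an interval variable, and ordinal items do not make a ten-item total ordinal. In that branch a group-by-time term tests the hypothesis properly. This is fair, and it is why the exposure of the GSES is only possible. But the text does not commit to it, and a non-normal GSES would be diverted. The secondary outcomes on this branch have no arm comparison either way.

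**The details belong in an analysis plan.** How normality is judged may well be left there. The choice of Friedman's test is not left there: the article names it, and a plan that followed the article would carry the error forward.

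**The simulated cases are selective.** This stands in part. The 3% figure needs TAU to worsen exactly as much as BEWARE improves, which the protocol does not expect. With TAU unchanged and BEWARE gaining 3.2, pooled Friedman rejects in 63–81%, although for time and not for group. The rate of exactly one significant arm also falls when the correlation is higher.

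**Nobody says the test will be run by arm.** True. The article does not say how it will be run, and the pooled version fails as well.

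**Mann-Whitney on change subtracts scores that are called ordinal.** Also true. It suits non-normal interval outcomes better than strictly ordinal ones.

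**Conclusion.** The rule is wrong as written. Friedman's test cannot contain the group factor that the plan lists, so every outcome on the non-parametric branch is left without a test of BEWARE against TAU. This follows from the structure of the test and needs no simulation assumption.

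Its reach is certain for whichever secondary outcomes fail the ANOVA conditions, and possible for the GSES. The consequences run both ways. A shared improvement of 2 points gives a significant pooled result in roughly 85–99% of trials with no treatment effect, over correlations of 0.5 to 0.7. A true difference can be missed almost entirely if the arms move in opposite directions. These percentages depend on the assumed correlation, trajectories and complete data.

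It must be fixed before analysis, because the trial's hypothesis is between arms and the primary outcome may fall under this rule.

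**What to change.** In the Data analysis section:

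1. Remove Friedman's test.
2. Fix the GSES analysis in advance as one baseline-adjusted comparison between arms, used whatever a normality check shows, with a permutation or bootstrap p-value as sensitivity analysis. Repeated-measures ANOVA with a group-by-time term would also test the arms. The essential step is to commit to one arm comparison beforehand; baseline adjustment is the recommended form.
3. For secondary outcomes that are ordinal or clearly non-normal, name a method with an arm term. For ordinal scores, use rank ANCOVA, an ordinal mixed model or a rank-based ANOVA-type test of arm by time. For non-normal interval measures, Wilcoxon-Mann-Whitney on change from baseline is also suitable.
4. State that any within-arm test over time is descriptive and will not be read as evidence of a treatment effect.

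The cost is a few sentences in the analysis section. No new data, visits or patients are needed.
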